## Abstract

**Background:**

The aging population in China is confronted with considerable challenges, with 14.71% of elderly individuals affected by mild cognitive impairment (MCI). The practice of Tai Chi has been demonstrated to enhance cognitive function, while sensory stimulation has been shown to facilitate neural activity. Nevertheless, the combined impact of Tai Chi and sensory stimulation on cognitive, sensory functions, and brain activation in older adults with MCI remains uncertain. This study aims to ascertain whether the integration of Tai Chi with sensory stimulation can facilitate more efficacious interventions for these outcomes.

**Methods and analysis:**

The TaiChi-MSS (Tai Chi and Multisensory Stimulation for Cognitive Function) study is a multi-center, randomized controlled trial (RCT) conducted in Suzhou and Shanghai, enrolling 88 participants aged 60 years or older with MCI. Participants will be randomly assigned to one of four groups: Tai Chi, multisensory stimulation, Tai Chi combined with multisensory stimulation or control. The intervention will last 6 months, with follow-up assessments at 3, 6, and 9 months. Primary outcomes include cognitive and sensory assessments, assessed using the Montreal Cognitive Assessment (MoCA), Mini-Mental State Examination (MMSE), domain-specific cognitive tests, Pure Tone Audiometry (PTA), and Sniffin’ Sticks Odor Identification Test. Secondary outcomes involve brain activation, measured through functional Magnetic Resonance Imaging (fMRI) scans. fMRI will be used to assess brain structure and connectivity changes, focusing on neuroplasticity. Data will be analyzed using mixed-effects models. The False Discovery Rate (FDR) will be the correction method for multiple comparisons to control for the expected proportion of false positives.

**Ethics and dissemination:**

This study was approved by the ethics committee of Shanghai University of Sport (No. 102772023RT200). The results of this study will be disseminated in peer-reviewed journals and presented at academic conferences.

## Introduction

China is one of the greatest countries that undergoes worldwide and rapid demographic progress, with the proportion of people aged 65 reaching 12.6% of the total population. In urban areas such as Shanghai, this proportion has already reached 21.8%, making it a “super-aged” city (Mitchell, 2015). This demographic shift presents a significant challenge, particularly with regard to the cognitive decline associated with aging. Alzheimer’s disease (AD), the most prevalent form of dementia, is typified by progressive cognitive decline, loss of functional autonomy, and considerable societal and economic burdens (Jack et al., 2024).

The findings of recent research indicate that Alzheimer’s disease commences its development approximately 10–15 years prior to the point at which a clinical diagnosis is made. This evidence underscores the vital importance of early intervention (Amieva et al., 2008; Bateman et al., 2012). Mild cognitive impairment (MCI) has become a key focus for preventive strategies, as it represents a transitional stage between normal cognitive aging and dementia (Jin et al., 2023; Rozzini et al., 2007). MCI is characterized by subjective cognitive complaints and measurable cognitive impairment, though functional abilities remain largely intact and do not yet meet the criteria for dementia (Anand and Schoo, 2024). In China, approximately 14.71% of the elderly population is estimated to be affected by MCI, underscoring the urgent need for effective intervention strategies (Xue et al., 2018). Especially at early preclinical stages such as early and stable MCIs (Zhou, 2021), these advancements hold significant promise for improving early diagnosis and intervention strategies.

In 2021, the US Food and Drug Administration granted accelerated approval to aducanumab for patients with MCI and mild dementia caused by Alzheimer’s disease (AD) (Terao et al., 2022). However, aducanumab was less well-tolerated than placebo, and its clinical outcomes did not meet expectations (Terao and Kodama, 2024). As a result, there has been a shift in focus toward non-pharmacological interventions. Among these, exercise, particularly aerobic and resistance training, has shown the potential to improve cognitive functions such as memory, executive function, and attention (Abrahamson et al., 2016; Cammisuli et al., 2017; Chow et al., 2021; Law et al., 2020; Loprinzi et al., 2019; Park et al., 2019; Song and Yu, 2019; Young et al., 2015; Zheng et al., 2016; Zhou, 2019). However, some studies indicate that the effects of these interventions on executive function and episodic memory are inconsistent (Ballesteros et al., 2024).

Tai chi emphasizes the coordination of the body, breathing, and mind, and as a potentially effective exercise method to improve brain health and slow down brain aging, Tai chi is attracting increasing attention (Loprinzi et al., 2013). Studies have shown that Tai Chi improves memory and executive function in individuals with MCI, potentially through mechanisms such as the increased expression of brain-derived neurotrophic factor (BDNF), which promotes neuroplasticity (Jasim et al., 2023; Zhang et al., 2023). However, despite growing interest, the exact mechanisms by which Tai Chi affects brain structure and function remain unclear, and further large-scale, long-term trials are necessary to confirm these effects (Miller and Taylor-Piliae, 2018; Wayne et al., 2018).

Recent studies have also explored the potential of sensory stimulation as an adjunct therapy for cognitive enhancement (Dimitriou and Tsolaki, 2017; Lykkeslet et al., 2014; Yang et al., 2021). Engaging multiple sensory modalities—such as vision, hearing, and smell, is hypothesized to enhance neural activity and improve cognitive function in patients with neurodegenerative conditions (Glachet and El Haj, 2020; Yang et al., 2021; Yoshii et al., 2019). Although promising, there is limited clinical evidence on the combined effects of Tai Chi and MSS on both cognitive and sensory function (Zhi-lei and Zhu, 2018). Moreover, the relationship between sensory decline and cognitive deterioration in MCI populations remains underexplored (Deal et al., 2016; Sayyid et al., 2024).

Thus, this study aims to investigate the effects of Tai Chi combined with multisensory stimulation on cognitive function, brain structure, and sensory function in older adults with MCI. We hypothesize that this combined intervention will lead to superior improvements in both cognitive and sensory outcomes compared to single-modality interventions, potentially through the “sensory-brain-cognitive” pathway. This research aims to provide critical insights into novel non-pharmacological interventions for MCI, contributing to the development of effective and scalable prevention strategies for dementia.

## Methods and analysis

### Objectives and study design

The TaiChi-MSS study is a randomized, controlled, single-blind trial conducted across multiple centers in Suzhou and Shanghai, in which the outcome assessors will be blinded to group assignments. Block randomization, with a fixed block size of four, will be used to allocate enrolled participants into one of four arms, ensuring balanced group allocation. A total of 22 participants will be assigned to each arm, with random allocation to the Tai Chi group (TCG), the Tai Chi combined with multisensory stimulation group (TMCSSG), the control group (CG), or the multisensory stimulation group (MSSG) according to a 1:1:1:1 allocation ratio. Outcome assessors will be masked to allocate and will not be involved in the interventions. Primary outcomes include assessing changes in cognitive function—such as attention, memory, language, visuospatial ability, and executive function—after a 24 weeks intervention period. Secondary outcomes involve evaluating sensory function through air conduction, pure tone hearing thresholds, and olfactory recognition levels, as well as analyzing the correlation between hippocampal subregion atrophy rates and volumes of auditory and olfactory regions using structural MRI.

As illustrated in Figure 1, this study will be conducted in three phases. Phase 1 is the development of the intervention, and Phase 2 comprises the screening, baseline assessment, and randomization of the participants and the execution of the multidomain intervention. Phase 3 is the approach modeling.

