### Intervention program

A factorial experimental design with four factors 4 × 4 will be used. All participants will be randomly assigned to one of the four groups: control group (CG), Tai Chi group (TCG), multisensory stimulation group (MSSG), or Tai Chi combined with multisensory stimulation group (TCMSSG). Key characteristics will be stratified; the stratification factors considered in this study include sex, years of education, and age to ensure that the groups are balanced.

The intervention will last for 6 months, followed by assessments at baseline, 3, 6, and 9 months. These assessments will include changes in overall cognitive function, measured through attention, memory, language, visuospatial ability, and executive function. Sensory function will be evaluated using air conduction, pure tone hearing threshold, and olfactory recognition tests. Functional MRI (fMRI) will be utilized to evaluate neural network connectivity and the effectiveness of the intervention on brain function.

The intervention for the Tai Chi groups (TCG and TCMSSG) will be based on exercise recommendations for older adults from the American College of Sports Medicine (ACSM). The 6 months intervention will include three weekly sessions, each lasting 50 min. The target heart rate (THR) will be calculated using the reserve heart rate percentage method (Table 2):

**TABLE 2 T2:** Exercise intensity intervention program [Tai Chi group (TCG) and Tai Chi combined with multisensory stimulation group (TCMSSG)].

Elements of intervention	Initial stage (4 weeks)	Mid-term (10 weeks)	Late stage (10 weeks)
Intensity of exercise	45% 55% HRmax	55% 65% HRmax	65% 75% HRmax
Frequency of movement	3 times a week	3 times a week	3 times a week
Duration	40 60 min	50 70 min	50 70 min

THR=(HRmax-HRrest)×intensity⁢(45%-75%)+

HRrest⁢(Lindenberger, 2008).

Additionally, the Borg Rating of Perceived Exertion (RPE) scale will be used to monitor participants’ subjective fatigue levels during the sessions.

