### Statistical analysis

Statistical Package for Social Sciences (SPSS) software (version 23.0) will be used for statistical analysis. An alpha level of (0.05) will be considered for all statistical tests. Two-sided *P*-values of (0.05) and (80%) power indicate statistical significance (Schulz et al., 2010). A mixed effect model will analyze the results and be employed for statistical analysis of the variance of the pretest (baseline score) and posttest (3, 6, 9 months) in the four groups. All mental, cognitive, sensory, and physical outcome measures will be used for statistical analysis. Discovery Rate (FDR) correction will be used for *post hoc* analysis.

Given the variety of cognitive and fMRI outcome measures, we will apply the False FDR to control for multiple comparisons (Genovese et al., 2002). Bonferroni correction will be used only if necessary for specific hypotheses with fewer comparisons, but FDR will be the primary approach (Alspach, 1996). An intention-to-treat (ITT) approach will be employed to handle missing data (Gupta, 2011; Little, 2024). Multiple imputations will be applied for missing cognitive data. Participants with incomplete or poor-quality fMRI data, such as those affected by motion artifacts, will be excluded from the fMRI analysis but kept in the cognitive analysis. Specific handling of missing data will depend on the outcome type.

Functional MRI (fMRI) will be utilized to evaluate neural network connectivity and the effectiveness of the intervention on brain function. Pearson correlation analysis will be conducted to assess the relationship between hippocampal subregion atrophy and the volumes of auditory and olfactory regions using structural MRI data. Similarly, Pearson or Spearman correlation coefficients will be calculated, depending on the distribution of the data, to explore the associations between fMRI-derived connectivity metrics and cognitive and sensory outcomes. These analyses aim to uncover potential neural mechanisms underlying the effects of the interventions. A sensitivity analysis will be performed by varying hypothetical dropout rates and effect sizes to assess their impact on the statistical power and required sample size (Little, 2024).

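### The published fixed block of four for four arms makes the last allocation in each block predictable, and the stated 22 per arm, the strata and centre are not reconciled

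*Protocol article*

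**What the plan says.** The Protocol article describes the randomisation in two places.

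- **Objectives and study design.** "Block randomization, with a fixed block size of four, will be used to allocate enrolled participants into one of four arms". Allocation is "according to a 1:1:1:1 allocation ratio", and "A total of 22 participants will be assigned to each arm". No strata are mentioned here. The masking statement is: "single-blind trial conducted across multiple centers in Suzhou and Shanghai, in which the outcome assessors will be blinded to group assignments".
- **Intervention program.** This section introduces stratification: "the stratification factors considered in this study include sex, years of education, and age to ensure that the groups are balanced". It gives no levels or cut-points and does not name centre, although the trial is "conducted across multiple centers in Suzhou and Shanghai".

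The four arms in the Intervention program section are Tai Chi, Tai Chi with music and diffused oils, music and oils alone, and no exercise intervention. Neither section says how the allocation list is held or released.

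**The concern.** When the block size equals the number of arms, each block is one permutation of the arms, and the choices left shrink with every allocation made. The size is fixed and in print, so anyone who learns recent allocations can work out what remains. Here they can be learned locally, because a participant or instructor cannot mistake Tai Chi for an aroma session or for no intervention.

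The risk is selective or timed enrolment. Some entry criteria call for judgement, such as health problems that would make participation unsafe, or exercise limitations. A recruiter who foresees a Tai Chi slot could hold back a frailer candidate or bring forward a fitter one. Masked outcome assessment does not repair a selection that happens at entry.

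A second problem is that the two sections do not describe one scheme. A reader cannot tell whether there is a single list or several, and so whether 22 per arm is a guarantee or an aim. Sites deliver the intervention and may differ in participants, yet centre is not named as a balancing factor.

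**Working it through.** **Inputs from the Protocol article.** Four arms, 1:1:1:1, fixed block of 4, 22 per arm (Objectives and study design); 56 evaluable and 35% dropout giving about 88 (Sample size); strata by sex, years of education and age (Intervention program).

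**1. The plan's own total.** 56 / (1 − 0.35) = 86.2, so 87, rounded up to a multiple of four = 88 = 4 × 22. This reproduces. It is also 88 / 4 = 22 complete blocks, so one unstratified list gives exactly 22 per arm.

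**2. Predictability of a block of four.** Given the earlier allocations in the block, the best guess is right with probability 1/4, 1/3, 1/2 and 1 at positions one to four.

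- Mean: (1/4 + 1/3 + 1/2 + 1) / 4 = 0.521, against 0.25 by chance.
- Over 88 participants on one list: 88 × 0.521 = 45.8 correct guesses, against 22 by chance.
- Fully determined: one per block, 22 of 88 (25%).

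With stratified lists the same holds inside each stratum, but only completed blocks yield a determined allocation. With eight equal strata (assumed), about 1.5 participants per stratum fall in an unfinished block on average, leaving (88 − 8 × 1.5) / 4 = 19 complete blocks. So 22 is the upper limit.

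**3. Is 22 per arm compatible with the strata?** The article gives no levels. Assuming equal-probability strata, blocks of four within each, and 88 participants in total, simulation gives:

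| Strata | Chance of exactly 22 in every arm | Mean gap, largest minus smallest arm |
|---|---|---|
| 1 (no stratification) | 100% | 0 |
| 2 (for example two centres) | 42% | 1.2 |
| 8 (three binary factors) | 5 to 6% | 2.6 |
| 16 (three binary factors and two centres) | 2% | 3.7 |

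**4. Centre.** Assume one unstratified list serving two equal centres. Each arm's count at a centre averages 22 / 2 = 11. The simulated gap between the largest and smallest arm within a centre averages 4.8, with 95th percentile 8.

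**5. What varied block sizes would do.** Simulated lists of 88, with a guesser who knows the whole history and the possible sizes but not the size of the current block:

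| Block sizes | Determined allocations | Best-guess accuracy |
|---|---|---|
| 4, fixed | 22 of 88 (25%) | 52.1% |
| 4 and 8, mixed | about 6.5 of 88 (7%) | about 48.5% |
| 4, 8 and 12, mixed | about 3 of 88 (3.5%) | about 46% |

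Varied sizes remove most of the certainty but only a little of the average guessability. Concealment of the list has to do the rest.

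**The case against.** The strongest reply is that prediction is conditional. Someone enrolling participants must know the three earlier allocations in the same block and stratum. The article does not say that recruiters see allocations, and a condensed article may leave concealment to the full protocol. Screening and baseline assessment are listed before randomisation, which narrows the scope for selection. All of this stands, and it is why the figures above are upper limits. It does not remove the point, because the fixed, published block size is a stated rule rather than an omission.

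Three stronger readings are tempting, and the document does not support them.

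- **That the trial is open-label and every fourth enrolment is certain.** The article says single-blind with masked assessors. That participants and instructors are unmasked is a sound inference, but certainty depends on local knowledge of the block. With several strata, the determined allocation is not every fourth in enrolment order.
- **That blocking contradicts stratification.** Permuted blocks within strata are a standard method, so the sections are compatible in principle. What fails is the guarantee of 22 per arm and the clarity of the description. A gap of two or three participants is trivial for power.
- **That the analysis ignores the stratifiers and so inflates standard errors.** The Statistical analysis section says only "A mixed effect model will analyze the results" and names no covariates; a condensed article may leave these to the analysis plan. A reader might compute 1/√(1 − 0.10) = 1.05 to 1/√(1 − 0.30) = 1.20, that is standard errors 5 to 20% too wide, if covariates explain an assumed 10 to 30% of variance. That formula applies to a single cross-sectional comparison. In a group-by-visit contrast, stable person-level main effects largely cancel. A simulation with 88 participants, four visits and 30% of variance explained gave a ratio of unadjusted to adjusted standard errors of 1.000 with complete data and 1.005 with 35% dropout.

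It is also fair that the listed factors are introduced by a verb that need not be exhaustive, so centre could be a further one, and that leaving it out to avoid sparse strata in 88 participants is defensible. The article should say which applies.

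**Conclusion.** The concern holds in limited form. A fixed, published block of four for four equal arms is the most predictable permuted block available: 52% best-guess accuracy against 25%, and up to 22 of 88 allocations determined. These figures assume knowledge of the earlier allocations in the block. That is plausible because the interventions are evident, but it is not established, because concealment is undescribed.

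Separately, the two descriptions of the randomisation need reconciling. The stated 22 per arm follows from one unstratified list and is unlikely to be met exactly with blocks inside strata: about 5 to 6% of lists, mean arm gap about 2.6, assuming eight equal strata. Centre is not among the named stratifiers of a multi-centre trial. No conclusion about the analysis model or its standard errors follows.

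**What to change.** 1. For participants not yet randomised, replace the fixed block with randomly varied sizes, for example 4 and 8, from a concealed central list. Do not disclose the sizes to recruiting staff.
2. Describe one scheme in one place: whether lists are stratified, by which factors and levels, and how the list is concealed.
3. Stratify by centre and keep other strata few, or use minimisation with a random element.
4. Restate 22 per arm as a target.

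The cost is a new list for the remaining participants, some rewording, and a possible arm imbalance of a few participants. The study started on 1 May 2024, so few participants may remain. In that case the useful step is to report which scheme was used, how it was concealed and how centre was handled.

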**Secondary outcomes**	
Brain activation	Structural, and resting state functional magnetic resonance imaging (fMRI) data will be acquired using 3.0 Tesla scanner

At least five participants from each group will be randomly selected to undergo structural and resting-state functional magnetic resonance imaging (fMRI) using a 3.0 Tesla scanner. Structural MRI will allow for detailed assessment of brain anatomy, focusing on changes in brain volume, particularly in regions associated with cognitive function, such as the hippocampus and prefrontal cortex. Resting-state fMRI will assess brain connectivity and activation patterns without the need for task-based stimuli, making it ideal for observing intrinsic brain network activity (Dickerson and Sperling, 2008). The baseline scans will establish a reference point for each participant’s brain structure and function, while the post-intervention scans will reveal how the multi-domain intervention influences brain changes over time.

As part of the baseline characteristics assessment, participants will receive written feedback on their medical and health parameters, which include blood pressure (systolic and diastolic), blood glucose (fasting or random), body mass index (BMI), heart rate (HR), oxygen saturation (SpO_2_), and basic physical activity level (assessed through a questionnaire or pedometer). Participants will be advised to consult their doctor for appropriate medical management if any concerns are identified, such as high blood pressure, hyperglycemia, abnormal BMI, or low oxygen saturation.

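### The structural-MRI secondary outcome is defined as a correlation between imaging measures, which does not estimate the intervention effect on brain structure that the protocol states as an aim

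*Protocol article*

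**What the plan says.** The Introduction states that the study will "investigate the effects of Tai Chi combined with multisensory stimulation on cognitive function, brain structure, and sensory function in older adults with MCI". The text below Table 1 (Baseline measurement) plans structural MRI before and after the intervention, looks at change in brain volume, and says that "the post-intervention scans will reveal how the multi-domain intervention influences brain changes over time".

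The section on objectives and study design describes the structural-MRI secondary outcome differently, as "analyzing the correlation between hippocampal subregion atrophy rates and volumes of auditory and olfactory regions using structural MRI". The Statistical analysis section repeats this: "Pearson correlation analysis will be conducted to assess the relationship between hippocampal subregion atrophy and the volumes of auditory and olfactory regions". It names no other analysis of structural MRI data, and this one has no group term.

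The four-group comparison is a mixed-effects model, "employed for statistical analysis of the variance of the pretest (baseline score) and posttest (3, 6, 9 months) in the four groups". The next sentence reads "All mental, cognitive, sensory, and physical outcome measures will be used for statistical analysis". Imaging is not in that list.

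The abstract says "Secondary outcomes involve brain activation, measured through functional Magnetic Resonance Imaging (fMRI) scans". It then adds that imaging will assess changes in brain structure and connectivity, and that mixed-effects models will be used for the data. Table 1 lists structural and resting-state MRI data under the label of brain activation.

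**The concern.** In a randomized four-arm trial, an effect on brain structure is a difference between arms in a structural measure. A correlation between two imaging measures is a different quantity. It has no value for an individual participant, and it says how the measures vary together, not whether either differs by arm. As defined, it also pairs a change (atrophy rate) with a level (volume), so change in the auditory and olfactory regions is not itself part of the outcome.

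Two things are at stake. If the outcome definition is followed literally, the structural part of the aim is reported without an effect estimate. And because the Statistical analysis section presents the correlations as a route to the mechanisms behind the intervention effects, a non-zero correlation could be read as support for the sensory-brain-cognitive pathway. Such a correlation can exist when the interventions have done nothing.

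**Working it through.** **1. The plan's own imaging figure.** Sample size gives 36 participants for imaging, 20% dropout and 44 after adjustment. 36 × 1.20 = 43.2, rounded up to 44; 36/(1 − 0.20) = 45. The stated 44 is reproduced to within one participant. The base of 36 cannot be recomputed, because the text at hand shows no effect size or power figure for imaging. With 1:1:1:1 allocation, 44 is 11 per arm and 36 is 9 per arm.

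**2. The statements side by side.**

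- Introduction: an effect on brain structure (needs an arm comparison).
- Text under Table 1: volume change, and the intervention's influence on it (needs an arm comparison; no model or contrast named).
- Objectives and study design: a correlation (no arm comparison).
- Statistical analysis, structural MRI: the same correlation (no arm comparison).
- Abstract: structural change, followed by a general sentence on mixed-effects models (no structural variable, region, time point or contrast).

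The only two places that name a structural quantity together with an analysis both give the correlation.

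**3. Does the correlation respond to an arm effect?** Assumptions: 9 per arm, correlation 0.3 within arms, and one measure shifted by s SD in one of the four arms. With x standard normal, y = 0.3x + √(1 − 0.09)·e + s in the shifted arm. If the correlation is taken over all participants, the shift adds s² × (1/4) × (3/4) = 0.1875s² to the variance of y, so r = 0.3/√(1 + 0.1875s²):

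- s = 0: 0.300
- s = 0.5: 0.3/√1.0469 = 0.293
- s = 1.0: 0.3/√1.1875 = 0.275

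In 4,000 simulated trials for each shift, the mean correlation was 0.295, 0.291 and 0.273. A four-arm F-test on the shifted measure rejected in 5%, 15% and 51% of the same trials. If both measures shift by 1 SD in the same arm and direction, the correlation does rise, to (0.3 + 0.1875)/1.1875 = 0.41, but it still does not show how far either measure differs between arms. Calculated within each arm, the correlation is unaffected by any such shift.

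**4. What an arm comparison could show.** Two-sample t-test, two-sided 0.05, df = 2n − 2, noncentrality d√(n/2); power is the probability that the noncentral t exceeds the critical value. The difference d detectable with 80% power is:

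- 5 per arm (the minimum in the text under Table 1): d = 2.02, noncentrality 2.02 × √2.5 = 3.19
- 9 per arm: d = 1.41, noncentrality 1.41 × √4.5 = 2.99
- 11 per arm: d = 1.26, noncentrality 1.26 × √5.5 = 2.95

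Power at these three sizes is 10%, 17% and 20% for d = 0.5, and 20%, 36% and 43% for d = 0.8. The values of d are assumptions, and FDR correction would lower these powers. The eligibility section can also be read as having every enrolled participant scanned at baseline. At 22 per arm without dropout, the detectable d would be 0.86.

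**The case against.** The strongest reply is that a between-arm analysis is plausibly intended and only badly linked. The abstract puts structural change next to the mixed-effects sentence. The text under Table 1 plans volume change from repeat scans. The FDR paragraph covers fMRI outcome measures. The analysis plan, which may name the model and contrast, is not at hand. The Introduction's hypothesis concerns cognitive and sensory outcomes, with the brain as a possible pathway, and the correlations are presented as mechanism work. Finally, the proposed comparison would have low power.

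Much of this stands, and it limits the point in four ways.

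- A reader might infer that brain structure has no test at all. The abstract and the text under Table 1 do not support that. The sentence listing mental, cognitive, sensory and physical measures does not say that imaging is left out of the mixed model.
- A reader might infer that the correlation pools all participants. The article does not say whether it is pooled, within arm or adjusted for arm. None of these estimates a difference in volume between arms.
- A reader might infer that Table 1 names a different outcome. Its label is brain activation, but its entry includes structural MRI data.
- A reader might expect the correlation to be zero if only hippocampal atrophy responded. That needs no association within arms, which the article does not state; volumes that do not change can still correlate with atrophy.

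The reply does not remove the mismatch. The outcome definition is the protocol's own, so this is not detail left to the analysis plan.

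**Conclusion.** The point holds in limited form. The structural-MRI secondary outcome, and the only structural analysis named, do not estimate the effect on brain structure that the Introduction and the text under Table 1 set as the purpose. The abstract, the objectives section and Table 1 also describe the imaging secondary outcome differently. This is a conflict between a stated aim and a stated outcome. It does not show that no arm comparison will be made.

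The correlation's weak response to treatment (0.295 to 0.273) rests on an assumed within-arm correlation of 0.3, a shift in one measure and one arm, and calculation over all participants. The primary cognitive outcomes are not affected.

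Nor should the arm comparison be oversold. A reader might infer good power from combining arms into factorial main effects of 22 versus 22. But if the combined arm differs from control by 1 SD with equal additive effects, each main effect is 0.5 SD, and power is about 37%.

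**What to change.** - Define the structural secondary outcome as each participant's change from baseline to the post-intervention scan, at a named time, in named volumes: hippocampal subregions, auditory regions and olfactory regions.
- Compare arms on this change with the planned mixed-effects model. Report estimates with confidence intervals, labelled exploratory.
- Keep the correlation as an exploratory mechanism analysis, state whether it is pooled, within arm or adjusted for arm, and say that it is not evidence of an intervention effect.
- Align the abstract, the objectives section, Table 1 with the text below it, and the Statistical analysis section.
- Reconcile the number to be scanned: 44 under Sample size, at least five per group under Table 1, and the baseline scan described in the eligibility section.

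The cost is rewording and further runs of a planned model on scans already planned. The downside is a few more tests in the FDR family and estimates of low precision.
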